## Abstract

**Background:**

Migraine is a primary neurological headache. Treatment of this condition includes medications; however, these medications, when given for a longer duration, can have side effects. If migraine is left untreated or undiagnosed, it is reported that around 2.5% of individuals with migraine may develop to have a chronic condition. This study aims to analyse the preliminary effectiveness of aerobic training on migraine pain level, sleep quality, quality of life, and resting-state brain waves among university students with migraine symptoms.

**Methodology:**

88 university students with migraine symptoms are the target participants. 4 of 5 on the Migraine Screen Questionnaire, 5 of 7 on the International Classification of Headache Disorders 3rd edition (ICHD-3), and both genders aged 18–40 years will be included. The participants with a score of more than or equal to 5 on the visual aura rating scale, diagnosed with a secondary headache, pregnancy, medication for neurological and cardiorespiratory conditions, and unwilling to participate will be excluded. Based on the disability questionnaire, the participants will be randomly assigned to either of the three groups. The primary outcome is resting-state electroencephalography (EEG) brain, and the secondary outcomes are sleep quality, quality of life, and migraine pain level. The post-test assessments will be performed at week 6.

**Result:**

After the primary EEG analysis using MATLAB, the amplitude, frequency, frequency band ratio, and power spectrum density will be analysed. Mixed design analysis and intention-to-treat analysis will be used to assess the efficacy of aerobic training.

**Discussion:**

Migraines can be unpredictable, sometimes occurring without symptoms. If underdiagnosed or over-looked, it encompasses a serious of long-term effects. Hence with appropriate intervention, the symptoms can be prevented from worsening. But there is an unmet need for evidence-based non-pharmacological approaches to complement pharmacotherapy in migraine prevention. Moreover, an exercise intervention may be more suitable for people with migraine considering their tendency toward inactivity. Although some studies developed exercise programs for untrained patients with migraine, the outcome was primarily in terms of exercise capacity rather than the primary characteristics and secondary brain wave/ sleep quality changes, indicating the need for this study.

## Background

Migraine is a primary neurologic headache [1], often accompanied by nausea, vomiting, photophobia, phonophobia, or vertigo, and may present with or without aura [2]. It is a prevalent disorder, affecting 15.1% of the world’s population [3]. It is a leading cause of disability worldwide; approximately half of those affected have such severe attacks that they cannot function normally in routine daily activities [4]. It also results in loss of quality of life (QoL) as well as having a significant impact on society as a whole [5]. Treatment of this condition includes medications such as beta-blockers, anticonvulsants, calcium channel blockers, tricyclic anti-depressants, and non-steroidal anti-inflammatory drugs [6]. Specifically, for abortive treatment, non-steroidal anti-inflammatory drugs (NSAIDs) are mainstay choices and have the greatest strength of evidence, followed by triptans, antiemetics, and ergotamines. The drugs of choice for preventive treatment are beta-blockers, antiepileptics, calcium channel blockers, and anti-depressants [1]. However, these medications, when given for a longer duration, can have side effects like constipation, cardiac conduction defects at higher doses, dizziness, flushing etc, depending on the medication used [1]. Additionally, recent evidence supports anti-CGRP antibodies for migraine, but the reported side effects include injection-site pain, pruritus, and erythema [7]. And also, currently, the headache disorder being a bio-psychosocial phenomenon, pharmacotherapy fails to address the psychological and social factors [5].

There are several hypotheses for migraine generation. The proposed mechanisms being: vasodilation of cerebral vasculature structure [8], drug-induced [9], hyperexcitability in cortical and brainstem areas [10,11], cortical spreading depression are responsible for migraine [12], and evidence also show trigeminal afferents projecting to meninges releasing pain mediators like substance P, calcitonin gene-related peptide, and neurokinin [13]. Occasionally, the pain is also due to hypertrophic nasal turbinates or deviated nasal septum irritating branches of trigeminal nerves [14].

The treatment for primary headaches is not common, it depends on severity, symptoms, and disability. Although medications were a common treatment choice, according to the Migraine research foundation, there are 3 main types of non-drug treatments for migraine. They are lifestyle advice, therapies, and exercises. Lifestyle advice includes seeing a doctor, maintaining a headache diary, sticking to the same eating and sleeping schedule [15]. Therapies include physical therapy, acupuncture, yoga, tai chi, massage, stress management, biofeedback, hypnotherapy, and cognitive behavioural therapy [16]. Especially, the EMG biofeedback has a beneficial effect on autonomous nervous system activity, renders individuals resilient to stressors, and possibly mediates a beneficial afferent vagus nerve stimulation. Through regular training, individuals experience a long-lasting reduction in muscle tension, a rise in peripheral skin temperature, and a lower heart rate [25], suggesting a feasible and cost-effective treatment option. Similarly, exercise programs are also frequently recommended to promote health, and the general guidelines include low-impact activities like tai-chi, yoga, isometrics, or band exercise [17]. Enkephalin, a natural anti-depressant released during exercise, aids in lowering stress levels, which is thought to be a primary migraine trigger. Therefore, to lessen the burden of daily medication intake, migraine patients can embrace exercise as a prophylactic or preventive treatment. Regular aerobic exercise, in particular, can help migraine sufferers by enhancing sleep quality, assisting those who are overweight or obese in losing weight, and lowering cardiovascular risk factors. Studies also found that exercise treatment significantly increased maximal oxygen uptake compared to the other treatments [18]. Hence both EMG biofeedback and exercises focus on the ability of the individual to relax during a stressful event, thereby improving physical fitness. Non-invasive neuromodulation constitutes a valuable approach with strong backing evidence, particularly in the case of sTMS and transcutaneous cranial nerve stimulation [19]. Behavioural treatment approaches can be considered an add-on to ongoing treatments and often offer a positive clinical improvement [20]. The use of non-pharmacological treatments for migraine represents an expanding clinical practice and an interesting area of research [19].

Habitual aerobic exercise has a major advantage of preventing or reducing symptoms of several chronic diseases and medical conditions [21]. Aerobic or cardiovascular exercise is a form of bodily movement fueled by aerobic energy-generating processes, where the energy demands of the exercise do not exceed the rate at which the cardiovascular system can supply oxygen to working muscles [22]. Aerobic exercises have already been proven to reduce the frequency, duration, severity or associated disability in migraine [21]. The physiology is that when one exercise, the body releases endorphins, the body’s natural painkillers and natural anti-depressants chemicals called enkephalins. According to Centre of Disease Control and Prevention (CDC), adults should exercise 150 minutes of moderate-intensity aerobic exercise and two or more days a week of muscle strengthening each week to relieve migraine or primary headaches. Similarly, a study comparing neck treatment and aerobic exercise concluded that five weeks of intervention for migraine patients responded with better outcomes [23]. According to the American migraine foundation, the exercise program should include cardiorespiratory fitness, flexibility exercises, and muscular strengthening. For migraines, mild to moderate aerobic exercise is highly recommended. But most of the studies’ primary outcome is only pain intensity, severity, duration, and frequency. Recent research found that the resting state brain waves were altered during the neuroimaging [24], and that the spatio-temporal dynamics exist in migraine patients during the resting-state. Moreover, the temporal dynamics, spatial changes, and clinical traits such as migraine disability interact [25], indicating the need for further analysis and appropriate treatment strategies. Hence this study aims to assess the preliminary effects of aerobic training on migraine pain level, sleep quality, quality of life, and resting-state brain waves compared with EMG biofeedback training and placebo group.

### Study goal and objective

If an earlier, migraine is left untreated or undiagnosed, it is reported that around 2.5% of individuals with migraine are considered to have a chronic condition, defined as presenting with more than 15 headache days within a month. Subclassifications of the disease (migraine with and without aura and chronic migraine) occur clinically at various severity levels and coexist with numerous comorbidities. For this reason, several studies encourage a multidisciplinary and tailored treatment approach for these patients [26,27]. This preliminary randomized control trial aims to analyse the effectiveness of aerobic training among university students with migraine symptoms. The main objective is to determine the preliminary effect of aerobic training on migraine pain level, sleep quality, quality of life, and resting-state brain waves compared with EMG biofeedback training and placebo.

The alternative hypothesis of this study will be the aerobic training will be superior to EMG biofeedback training and placebo group in improving migraine pain level, sleep quality, quality of life, and resting-state brain waves. The null hypothesis will be the aerobic training is same as to EMG biofeedback training and placebo group in improving migraine pain level, sleep quality, quality of life, and resting-state brain waves. Although the Migraine Research Foundation listed three main types of non-drug treatments for migraine: lifestyle advice, therapies, and exercises. Some common aerobic exercises such as walking, jogging, a behavioral weight loss program, cycling, and a combination of cross-training, walking, jogging, and cycling are suggested to be beneficial to migraine patients but there remains no specific protocol established till now. Hence, this study will contribute to the research field by establishing an aerobic training protocol for patients with migraine symptoms.

## Methodology

This study is a pilot randomized control trial with a pre-and post-test design that focuses on the preliminary efficacy of aerobic training among university students with migraine symptoms. The primary endpoint is resting-state electroencephalography (EEG). The secondary endpoints are sleep quality, quality of life, and migraine pain level. This study will be conducted at Physiotherapy Center, Universiti Tunku Abdul Rahman, Sungai Long Campus. The outcome measures will be performed at baseline and end of intervention (6^th^ week) to compare the data obtained. The study is approved by UTAR Scientific and Ethical Review Committee (U/SERC/188/2022). The informed consent form will be signed and dated before the start of the actual intervention. Parallel assignment intervention model will be used. The study is also registered with ClinicalTrials.gov Protocol Registration and Results System (Identifier: NCT05741775).

### Inclusion and exclusion criteria

The target participants for this research will be undergraduate and postgraduate students from Universiti Tunku Abdul Rahman. The participants who fulfil the following criteria will be recruited for the interventional phase. 4 of 5 on the Migraine Screen Questionnaire, and 5 of 7 on International Classification of Headache Disorders 3rd edition (ICHD-3). Both genders aged between 18–40 years. The participants with a score of more than or equal to 5 on the visual aura rating scale, diagnosed to have a secondary headache (headache attributed to the causative disorder example: infection, trauma, or injury to head/ or neck) [28], pregnancy, took medication for neurological conditions like stroke, multiple sclerosis and took medications for cardiorespiratory conditions like asthma, took medications for headache and unwilling to participate will be excluded.

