**Fig 5 pone.0291534.g005:**
[figure not shown]
Warm up and cool down exercise.

During the exercise, the subjective measure of how hard the participant feels during the activity is measured using Borg’s Rating of Perceived Exertion (RPE) [45,46].

Similarly, during aerobic training, the exercise intensity will correlate with how hard the activity feels. The objective measurement of exercise intensity using heart rate calculation method will be used in this study. To calculate the heart rate, the Karvonen method, otherwise called as heart rate reserve (HRR) formula, takes the resting heart rate into consideration by introducing the difference between maximum heart rate and resting heart rate. Using the Karvonen principle, the target heart rate will be calculated using the formula: [(max HR − resting HR) × %Intensity] + resting HR. The maximum heart rate (max HR) will be calculated using the formula: 220-age. The resting heart rate (resting HR) will be calculated by measuring pulse at rest. For moderate-intensity physical activity, the target heart rate should be between 64% and 76% of the maximum heart rate [47].

An elastic band secured around the head will apply local pressure over the area. Red color bands will be used since the target area is muscle around the chin or shoulder. This strengthening exercise will use a dynamic isometric thera-band exercise that will be performed in a sitting position with a single series/ set of 15 repetitions in forward, obliquely toward the right and left, and backward.

Kettler Computeranleitung Advanced display will be used to train static cycling. Upon starting the machine, a new user item will be created, and the desired heart rate will be entered. During training, the participant grips the detector and starts cycling, Borg’s RPE will be maintained at 11–14. The central graphic in the display shows whether the participant is within range or whether above or below the target range. The average exercise bike pedaling speed will be 50 to 60 rpm.

ProAction BH Treadmill G6700 instrument will be used for aerobic training. Following the target heart rate calculation, the participant will start to walk at a comfortable pace by griping the detector, and Borg’s Rating of Perceived Exertion (RPE) measures the physical activity intensity level will be maintained at 11–14, and the speed of walking will be at 4 mph and depending on RPE response the speed will be either be maintained or increased to 5 mph.

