#### Termination criteria

The termination criteria are based on ACSM guidelines for exercise testing/ prescription [49] and migraine trust [50]:

Absolute termination: Onset of moderate to severe angina [51], signs of poor perfusion: pale appearance to the skin, bluish discoloration, excessive cold and clammy skin, severe or unusual shortness of breath (modified Borg’s scale), ataxia (failure of muscle coordination), vertigo (an illusion of dizzying movement), visual or gait problems and confusion Migraine induced headache Relative termination: Any chest pain that is increasing shortness of breath (modified Borg’s scale), leg cramps/ fatigue, patients’ request.

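### The neurological and cardiorespiratory exclusions depend on medication and not on the condition, so a student with known but unmedicated disease can be allocated to the aerobic arm.

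*Protocol article*

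**What the plan says.** Under Inclusion and exclusion criteria, the article excludes participants who "took medication for neurological conditions like stroke, multiple sclerosis and took medications for cardiorespiratory conditions like asthma". The Methodology paragraph of the abstract gives the same rule in short form: "pregnancy, medication for neurological and cardiorespiratory conditions, and unwilling to participate will be excluded". In both places the trigger is medication. The body section gives no period over which its use counts.

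The same section does word other exclusions by condition. Pregnancy is one. Secondary headache is another: "diagnosed to have a secondary headache (headache attributed to the causative disorder example: infection, trauma, or injury to head/ or neck". It also has a separate exclusion for headache medication.

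Procedure and stages describes screening as the migraine questionnaires plus assessment against these exclusion criteria, followed by MIDAS grading and random allocation.

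The aerobic arm combines neck exercise, static cycling and treadmill walking. On intensity the article states: "The objective measurement of exercise intensity using heart rate calculation method will be used in this study". The target uses measured resting heart rate and an age-based maximum ("The maximum heart rate (max HR) will be calculated using the formula: 220-age"), and Borg RPE is held at 11–14 on both machines.

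Termination criteria begins: "Absolute termination: Onset of moderate to severe angina [51], signs of poor perfusion". It goes on to severe breathlessness, and Safety consideration tells participants to stop for chest pain, dizziness or shortness of breath. The Discussion lists cardiovascular disease, stroke and hypertension among the long-term comorbidities of migraine. The primary endpoint is resting-state EEG.

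**The concern.** Medication is an imperfect stand-in for disease. A criterion that sees only treated disease lets through a student who knows of a heart, lung or neurological condition but takes nothing for it. The protocol itself treats cardiac and respiratory events during exercise as foreseeable and links such conditions to migraine, so the gap sits where the document expects risk.

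Two things are at stake. The first is the safety of people allocated to the aerobic arm, the only arm that exercises. The second is the quality of the primary endpoint: a neurological condition can alter resting EEG, and Outcomes does not list such comorbidity among the confounders (pain level, gender, age, COVID-19).

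**Working it through.** The point rests on the wording of the rule and not on a figure, so the check applies the stated criteria to the possible cases and then asks whether another section closes any gap.

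**1. The stated exclusions, case by case**

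| Student at screening | Stated exclusion met |
|---|---|
| Cardiorespiratory condition, medicated for it | Yes, by medication |
| Known cardiorespiratory condition, no medication | None |
| Neurological condition other than migraine, medicated for it | Yes, by medication |
| Such a neurological condition, no medication, headache attributed to it | Yes, as secondary headache |
| Such a neurological condition, no medication, no attributed headache | None |
| Medication for such a condition in the past, now stopped | Unclear, no period given |

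Two rows have no exclusion and one cannot be decided.

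**2. Does another section close the gap before allocation?**

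- Procedure and stages screens with migraine instruments and these same criteria, so it inherits the gap.
- The secondary-headache exclusion closes it only where a headache has been attributed to the disease.
- Termination criteria and Safety consideration apply during sessions. The headache diary, which asks about chest pain and shortness of breath, is kept during the intervention phase. All three come after allocation.

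No described step closes the gap before entry.

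**3. Exposure in the aerobic arm**

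3 sessions per week × 6 weeks = 18 sessions, which matches the 18 under Compliance during the experimental study.

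**4. Scale**

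The planned total is 66 / (1 − 0.25) = 88, as stated under Sample size. Per arm this is 88 / 3 = 29.3 enrolled, or 66 / 3 = 22 after the planned dropout. One participant is therefore 1 / 29.3 = 3.4% of an enrolled arm, or 1 / 22 = 4.5% of completers. If one such participant's EEG change differs by d standard deviations from what it would otherwise be, the arm mean moves by d / 29.3, or d / 22 among completers. The document gives neither d nor the number of such participants. If there were 1 to 3 per arm, that would be 1 / 29 = 3.4% to 3 / 29 = 10.3%; this range is an assumption for scale only.

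**5. Direction of the EEG effect**

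Allocation is random, so such participants are spread across arms on average. Measurement is before and after, so a stable condition affects both recordings. What remains is extra variance and chance imbalance in small arms.

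**6. Sample size**

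Rewording the exclusion changes no input to the calculation; 66 and 88 are unaffected.

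**The case against.** The two statements of the exclusion agree with each other, and a medication criterion has its own purpose, because drugs can affect heart rate and EEG. This is a journal article: a readiness checklist, the screening form and the exact meaning of past use may sit in the full protocol. The exercise is of moderate intensity, in a physiotherapy centre, with RPE control and stopping rules, and the participants are aged 18–40.

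Much of this stands. The absence of a checklist is not a fault that can be shown from an article. The medication criterion should stay. The safeguards reduce the risk. None of it changes the stated rule, which turns on medication both times it appears.

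A reader might go further in several ways that the documents do not support:

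- **Heart-rate-lowering drugs invalidate the exercise target, so drug classes should be excluded for any indication.** The target also uses measured resting heart rate, and RPE steers intensity alongside it. The body section already excludes headache medication, which covers beta-blockers and antidepressants taken for migraine, and the cardiorespiratory medication rule covers beta-blockers taken for a cardiac condition. Only other indications remain, and a class-wide exclusion would be a debatable trade-off.
- **Unmedicated students are those at greatest risk.** Nothing shows that they carry more risk than the medicated students who are excluded.
- **Any remote past use excludes.** This rests on one verb tense in the body section. It is better treated as an ambiguity.

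**Conclusion.** The concern holds as a gap in a stated rule: a student with known but unmedicated cardiorespiratory or neurological disease is not excluded and can be allocated to the aerobic arm. It would be wrong to infer that such students will enter in any particular number. The document gives no prevalence, and in students aged 18–40 the number may be small.

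The weight lies on exercise safety in the aerobic arm, because the exercise safeguards act only after exposure. It would also be wrong to infer a biased EEG comparison. With random allocation and before-and-after measurement, the expected effect is noise and chance imbalance of unknown size. The conclusion assumes that the criteria are applied as written and that no unpublished screening step covers the condition itself. The wording should be changed; the design and sample size need no change.

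**What to change.** Reconcile the exclusion wording in the abstract and in Inclusion and exclusion criteria with the exercise arm, the EEG endpoint, the Termination criteria and the comorbidities named in the Discussion:

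- Keep the medication criterion, and add the known cardiorespiratory or neurological condition (other than migraine) whether or not it is medicated.
- State the period over which medication use counts.
- Leave the exact list of conditions and the period to the investigators.
- Ask about it in the screening questionnaire already distributed, before allocation, so that it applies equally to all three arms.

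If the full protocol already covers the condition, it is enough to bring the article's wording into line with it.

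The cost is a wording change and a short self-report item in an existing form. The downside is that a few more volunteers are screened out, a number that cannot be estimated from the document.
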